### Cessation of renal replacement therapy

RRT may be discontinued due to:

1. Withdrawal of renal support in the context of a change in the overall goals of care for the patient, or

2. Kidney function recovery with no need for RRT, assessed at least 48 hours after the last RRT session and defined by:

i. Decline in serum creatinine by ≥50 μmol/L on two blood tests separated by >12 hours with no RRT during the 48 hours from the last RRT session to the time of assessment; or

i. Urine output >6 mL/kg during any 12-hour period during the 48-hour period of evaluation, with most recent serum potassium <5.5 mmol/L and most recent serum bicarbonate >18 mmol/L.

### Co-interventions

The administration of volume expanders, inotropes, and vasopressors for hemodynamic support will be at the discretion of the ICU team. Vital signs and routine blood work will be performed and documented as per usual practice.

### Monitoring and follow-up

We will collect data on all RRT treatments, adverse events and serious adverse events (defined below) for 14 days after randomization. We will determine vital status and need for RRT among survivors at 90 days following randomization through chart review and direct contact with patients or SDMs, if necessary.

### Primary and secondary outcomes

Our primary outcome is protocol adherence, defined as >90% of participants adhering to their allocated treatment (that is, in the accelerated arm, starting RRT within 12 hours of eligibility; and in the standard initiation arm, starting RRT at least 12 hours following eligibility, considering patients who ultimately receive RRT). Compliance with protocol adherence will be captured for all randomized patients. For those allocated to the standard arm, we will ascertain the time of starting RRT (if started) relative to the time of fulfilling eligibility, and the indications for starting RRT. We will capture the specific reasons for non-compliance and crossover to starting RRT prior to 12 hours in those patients allocated to the standard arm.

Secondary outcomes include:

1. Proportion of eligible patients who are successfully enrolled in the trial (feasibility objective, >50% of eligible patients).

2. Proportion of enrolled patients for whom vital status and need for RRT can be determined at 90 days (feasibility objective, >95% of participants).

3. Serious adverse events potentially attributable to the study treatment, including death, vascular-access complications and complications associated with the delivery of RRT occurring up to day 14.

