Our objective is to conduct a Canadian multi-centerRCT in critically ill patients with severe AKI, comparing the effect of accelerated versus standard RRT initiation on 90-day mortality and dialysis dependence among 90-day survivors. To support this trial, we propose to perform a pilot trial to evaluate protocol adherence, estimate recruitment rates, confirm that meaningful separation in the timing of RRT between treatment arms can be achieved, and evaluate safety.

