### Inclusion criteria

The inclusion criteria are designed to identify a population of critically ill adults with severe AKI who have an increased likelihood of receiving RRT during their hospitalization, but who do not have urgent indications for the initiation of RRT at the time of fulfilling eligibility criteria. All six criteria must be fulfilled at the time of screening:

1. Age ≥18 years.

2. Admission to an ICU.

3. Evidence of kidney dysfunction (serum creatinine above the upper threshold of normal for commercially available laboratory assays (women ≥100 μmol/L; men ≥130 μmol/L)

4. Evidence of severe AKI based on at least two of the following three criteria:

i. A 2-fold increase in serum creatinine during hospitalization or from a known pre-hospitalization baseline with current creatinine no less than 25 μmol/L below peak (consistent with the Risk, Injury, Failure, Loss, End-stage renal failure (RIFLE) INJURY category of AKI);

i. Oliguria as defined by urine output <6 mL/kg over the preceding 12 hours (consistent with RIFLE category of AKI);

i. If only one of two above criteria for severe AKI are met and all other eligibility criteria are fulfilled, a whole-blood Cardiorenal Neutrophil Gelatinase-Associated Lipocalin™ (NGAL)(Alere Inc., San Diego, CA, USA) ≥400 ng/mL.

5. Likelihood that an absolute indication for RRT will not arise in the subsequent 24 hours based on the most recent blood laboratory values:

i. Serum potassium ≤5.5 mmol/L, and

i. Serum bicarbonate ≥15 mmol/L.

6. Central venous pressure ≥8 mmHg. The rationale for this criterion is to ensure adequate volume resuscitation and mitigate enrollment of patients with hypovolemia or AKI that will readily improve with fluid administration.

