### Interventions

Accelerated RRT initiation (experimental arm):a catheter will be placed by the treating ICU or Nephrology team and RRT initiated as soon as possible, and within 12 hours of eligibility. This 12-hour window includes the time needed to obtain consent.

Standard RRT initiation (control arm):the study team will follow patients for 7 days to identify potential indications for RRT. For patients with persistent AKI (serum creatinine has not declined by more than 50% from value at time of eligibility), the protocol discourages RRT initiation unless one or more of the following criteria are met:

1. Serum potassium ≥6.0 mmol/L, or

2. Serum bicarbonate ≤10 mmol/L, or

3. Severe respiratory failure, defined as arterial partial pressure of oxygen(PaO_2_)/inspired oxygen fraction(FiO_2_)<200 and bilateral infiltrates on the chest radiograph, or

4. Persistent AKI (as defined above) 72 hours after eligibility.

Notwithstanding these recommendations, RRT in the control arm may be commenced at anytime, provided >12 hours have elapsed since the patient met eligibility criteria, at the discretion of the attending physician(s). This will not be considered a protocol deviation. If this occurs, the physician will be asked to specify the primary reason for initiating RRT on that day. If RRT is initiated within 12 hours of eligibility, the clinician will also be asked to provide primary reason(s) for this protocol violation.

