### Analysis

Analysis will be intention-to-treat. The primary feasibility analysis will evaluate the proportion (95% CI) of all randomized patients adhering to their allocated treatment. The secondary feasibility analyses will evaluate the proportion (95% CI) of all screened eligible participants who are enrolled, and the proportion (95% CI) of enrolled patients having vital status and RRT dependence at 90 days ascertained. The secondary safety analysis will evaluate differences in the incidence of adverse events between the accelerated and standard groups. Tertiary analyses of patient-centered and health-resource utilization outcomes between the groups will be performed, including mortality through day 90, need for RRT through day 90, a composite of major adverse kidney events (MAKE), duration of ICU stay, duration of hospitalization and hospital readmission through day 90.

Descriptive statistics, boxplots and histograms will be used to analyze individual baseline variables by accelerated or standard arms. Normally or near normally distributed, non-correlated variables will be reported as means with SD and compared using the appropriate Student’s *t*-test. Non-normally distributed, non-correlated continuous data will be reported as medians with IQRs and compared using the Mann Whitney *U*-test. Non-correlated categorical data, including the tertiary analyses such as mortality and need for RRT, renal recovery and hospital mortality, will be reported as proportions and compared using Fisher’s exact test. Normally distributed correlated data will be analyzed by repeated measures analysis of variance (ANOVA). Non-normally distributed correlated data will be analyzed by the Friedman test. Correlated categorical data will be analyzed by generalized estimating equations. A *P*-value <0.05 will be considered significant. All statistical tests will be two-sided.

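### The >90% adherence target is set on both arms pooled, so it can be met with accelerated-arm adherence of 82–86%, and it cannot test the stated aim of separation in RRT timing

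*Protocol article*

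**What the plan says.** The Primary and secondary outcomes section sets a single threshold: "Our primary outcome is protocol adherence, defined as >90% of participants adhering to their allocated treatment". It defines adherence by arm. An accelerated-arm patient adheres if RRT begins inside the 12-hour window after eligibility. For the other arm the definition reads: "in the standard initiation arm, starting RRT at least 12 hours following eligibility, considering patients who ultimately receive RRT". The Analysis section then uses one proportion: "The primary feasibility analysis will evaluate the proportion (95% CI) of all randomized patients adhering to their allocated treatment". No arm-specific target is given.

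For the standard arm, the Interventions section says that "RRT in the control arm may be commenced at anytime, provided >12 hours have elapsed since the patient met eligibility criteria", at the physician's discretion, and adds: "This will not be considered a protocol deviation". The inclusion criteria select for "Likelihood that an absolute indication for RRT will not arise in the subsequent 24 hours based on the most recent blood laboratory values", and exclusion criterion 8 removes patients whose clinician considers immediate RRT mandatory.

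The Background gives a further aim of the pilot: to "confirm that meaningful separation in the timing of RRT between treatment arms can be achieved". The Sample size section plans for a difference of at least 24 hours in time to RRT. It also gives a 95% CI of 79 to 96% around 90% adherence with n=100, and calls the lower limit the minimum acceptable for the definitive trial.

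**The concern.** The pilot has one primary success criterion, and it averages a hard task with an easy one. In the accelerated arm, consent, catheter placement and the start of RRT must all fit into 12 hours. In the standard arm, any start after 12 hours is adherent, whether or not a listed criterion is met. Where standard-arm adherence is high, it offsets shortfalls in the arm whose feasibility is in real doubt.

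The same criterion says little about separation. Both arms share the 12-hour boundary, so adherence records only on which side of it a start falls. Separation is a stated aim with a planning figure, but it is neither a listed outcome nor a named analysis. The pilot could therefore be declared feasible without an explicit judgement on either matter, and the definitive trial depends on both.

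**Working it through.** **Inputs.** From the protocol article: n=100 allocated 1:1, so 50 per arm; target >90%; minimum acceptable 79%; planned timing difference 24 h; RRT receipt of 50 to 70% in severe AKI (Background). Assumed: standard-arm adherence of 96%, 98% or 100%, because the article gives no expected value.

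**1. The stated precision.** Wilson 95% intervals:
- 90/100: 82.6 to 94.5%. The Wald, Clopper-Pearson, Agresti-Coull and Jeffreys intervals at n=100 do not give 79 to 96% either.
- 45/50: 78.6 to 95.7%, which rounds to the stated 79 to 96%.
- The article's other two intervals also reproduce with Wilson: 95/100 gives 88.8 to 97.8% (stated 89 to 98%), and 100/200 gives 43.1 to 56.9% (stated 43 to 57%).

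So the stated adherence interval, and the 79% minimum taken from it, fit one arm of 50, while the planned analysis pools 100.

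**2. Lowest accelerated-arm result that passes.** With all randomized patients counted, passing needs (a + s)/100 > 0.90, that is a + s ≥ 91, where a and s are the adherent counts in the accelerated and standard arms.

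| Standard arm | Accelerated arm needed |
|---|---|
| 50/50 (100%) | 41/50 (82%) |
| 49/50 (98%) | 42/50 (84%) |
| 48/50 (96%) | 43/50 (86%) |
| 45/50 (90%) | 46/50 (92%) |

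If only standard-arm RRT recipients count, 50 to 70% of 50 is 25 to 35 patients. With all of them adherent:
- 35 recipients: (42 + 35)/85 = 90.6%, so 42/50 (84%) is needed.
- 30 recipients: (43 + 30)/80 = 91.3%, so 43/50 (86%) is needed; 42 gives exactly 90.0%, which is not above 90%.
- 25 recipients: (43 + 25)/75 = 90.7%, so 43/50 (86%) is needed.

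**3. Intervals at the edge.** Accelerated 41/50 = 82%, Wilson 69.2 to 90.2%. Pooled 91/100 = 91%, Wilson 83.8 to 95.2%. The pooled lower limit clears 79%; the accelerated-arm lower limit does not.

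**4. Probability of passing at a true accelerated adherence of 82%.** A ~ Bin(50, 0.82) and S ~ Bin(50, pS), independent.

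| Rule | Probability |
|---|---|
| Pooled, P(A + S ≥ 91), pS = 1.00 | 0.59 |
| Pooled, pS = 0.98 | 0.45 |
| Pooled, pS = 0.96 | 0.32 |
| Recipients only, 35, all adherent: P(A ≥ 42) | 0.44 |
| Recipients only, 25 or 30, all adherent: P(A ≥ 43) | 0.30 |
| Accelerated arm alone: P(A ≥ 46) | 0.04 |

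**5. Separation.** If every accelerated patient starts just before 12 h and every standard-arm recipient just after, adherence is 100% and the timing difference is minutes, against the 24 h used for planning. This is a limiting case. It shows that the adherence rule sets no lower bound on separation.

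**The case against.** Several points on the other side stand.

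- **The masking is bounded.** With 50 per arm, accelerated adherence below 41/50 cannot pass, and 82% as a point estimate lies above the 79% minimum. Only its confidence interval falls below. A reader might infer that the pooled rule lets a collapsed accelerated arm through, or that 82% adherence would make the definitive trial uninformative. The article supports neither.
- **Near-complete standard-arm adherence is an inference.** Inclusion criterion 5 screens only potassium and bicarbonate. The respiratory criterion for the standard arm is not screened at entry, and the protocol provides for recording reasons for early starts. If standard-arm adherence were 90%, pooling would give no help: the accelerated arm would need 46/50.
- **The standard-arm definition is qualified by receipt of RRT.** If patients who never start are left out, the carry-over shrinks. It does not vanish, as step 2 of the working shows. The qualification also conflicts with the Analysis section, which counts all randomized patients.
- **Full adherence does not mean no separation.** That reading is tempting but literally wrong, because adherent starts fall on opposite sides of 12 hours. The protocol also asks for accelerated RRT as soon as possible and discourages standard-arm RRT without a listed criterion. Start times are recorded, so a very small difference would be visible to anyone who looked.
- **An article may leave detail to the full protocol or SAP.** That covers the test and the display. It does not cover the target and analysis set, which the article states, or the outcome list, which omits a stated aim.

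**Conclusion.** The point holds in bounded form. The pooled >90% target can be met with accelerated-arm adherence of 82–86% when standard-arm adherence is 96–100%. At a true 82%, that happens with probability 0.32–0.59 counting all randomized patients, or 0.30–0.44 counting 25–35 standard-arm recipients who all adhere, against 0.04 for a target on the accelerated arm alone. These figures rest on 50 per arm, independent binomial outcomes and the assumed standard-arm adherence. The recipient range takes the Background's 50 to 70% as applying to this population.

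Separately, adherence cannot answer the separation aim, and the outcomes and named analyses contain nothing that does. Both matters should be corrected. Neither invalidates the pilot, since the data needed are already to be collected.

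**What to change.** 1. Report adherence with a 95% CI by arm, and judge the >90% target in the accelerated arm. At n=50 this matches the stated 79 to 96% precision. Report the standard-arm and pooled figures alongside.
2. State one denominator for the standard arm, reconciling the Primary and secondary outcomes section (RRT recipients) with the Analysis section (all randomized patients).
3. Name the between-arm difference in time to RRT initiation as a feasibility outcome, read against the 24-hour planning figure. Choose one time origin: the Sample size section counts from randomization, the adherence definition from eligibility. Say how standard-arm patients who never start RRT are handled, for example a comparison among recipients plus a cumulative-incidence display by arm.

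**Cost.** Wording and analysis only; no extra patients and no change to any treatment rule. The accelerated-arm interval is wider than the pooled one, and the target is harder to meet: at a true 95% adherence, P(A ≥ 46 of 50) is 0.90, against 0.97 for the pooled rule with 95% in both arms. Requiring both arms to exceed 90% would be stricter still (0.90 × 0.90, about 0.80) and is not needed.

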**Methods/design:**

This is an open-label pilot randomized controlled trial. One hundred critically ill patients with severe acute kidney injury will be randomly allocated 1:1 to receive “accelerated” initiation of renal replacement therapy or “standard” initiation at 12 centers across Canada. In the accelerated arm, participants will have a venous catheter placed and renal replacement therapy will be initiated within 12 hours of fulfilling eligibility. In the standard initiation arm, participants will be monitored over 7 days to identify indications for renal replacement therapy. For participants in the standard arm with persistent acute kidney injury, defined as a serum creatinine not declining >50% from the value at the time of eligibility, the initiation of RRT will be discouraged unless one or more of the following criteria are fulfilled: serum potassium ≥6.0 mmol/L; serum bicarbonate ≤10 mmol/L; severe respiratory failure (PaO_2_/FiO_2_<200) or persisting acute kidney injury for ≥72 hours after fulfilling eligibility. The inclusion criteria are designed to identify a population of critically ill adults with severe acute kidney injury who are likely to need renal replacement therapy during their hospitalization, but not immediately. The primary outcome is protocol adherence (>90%). Secondary outcomes include measures of feasibility (proportion of eligible patients enrolled in the trial, proportion of enrolled patients followed to 90 days for assessment of vital status and the need for renal replacement therapy) and safety (occurrence of adverse events).

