### Adverse events

Adverse events that are potentially attributable to the study treatment, including death, vascular-access complications (that is, hemorrhage, thrombosis, or infection) and complications associated with the delivery of RRT (that is, dialysis-associated hypotension, electrolyte abnormalities, and arrhythmias) will be documented during the first 14 days after randomization (Table 2). In addition, all serious adverse events that occur within 14 days after randomization are to be documented and reported, regardless of direct connection to the study. A serious adverse event is defined as: 1) any event that is fatal or immediately life-threatening, permanently disabling, severely incapacitating, or requires prolonged inpatient hospitalization, or 2) any event that may jeopardize the patient and requires medical or surgical intervention to prevent one of the outcomes listed above. We will track all adverse events until resolution or day 90, whichever comes first.

**Table 2 T2:** Reportable adverse events

**Related to renal replacement therapy (RRT)**	**Related to central venous catheter (CVC)**
RRT-associated hypotension:	Hemorrhage at the site of CVC insertion:
Drop in blood pressure requiring one of: initiation of a vasopressor during RRT session, or need to escalate dose of a vasopressor during the RRT session, or premature discontinuation of RRT session, or any other intervention to stabilize blood pressure.	Bleeding requiring transfusion of ≥1 unit(s) of packed red blood cells and/or surgical intervention/repair within 12 hours following insertion
Severe hypophosphatemia:	CVC-associated bloodstream infection:
Serum phosphorus <0.5 mmol/L	Bacteremia in 2 blood culture sets with no proven alternative source for bacteremia or culture-positive recovery of the same organism from the dialysis catheter upon removal
Severe hypokalemia:	Ultrasonographically-confirmed thrombus attributed to CVC
Serum potassium <3.0 mmol/L	
Severe hypocalcemia:	Pneumothorax (for catheters placed in the internal jugular or subclavian positions)
Albumin-adjusted serum calcium <2.00 mmol/L or ionized calcium <1.00 mmol/L	
Allergic reaction	Hemothorax (for catheters placed in the internal jugular or subclavian positions)
Arrhythmia during dialysis:	Air embolism
New atrial (excluding sinus tachycardia or sinus arrhythmia) or ventricular arrhythmia that develops during RRT and was not present prior to initiation of RRT	

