## Discussion

The optimal timing of RRT initiation for severe AKI is currently unknown. Data from observational studies and recent systematic reviews [9,10,26-31] suggest that earlier commencement of RRT may benefit patients, but high-quality evidence to support this decision is currently lacking. Prior to starting a large, definitive RCT addressing this question, a pilot study is necessary to determine the feasibility of participant recruitment and protocol implementation in addition to assessing safety.

Strengths in the design of our pilot trial include carefully defined feasibility objectives, a clinically grounded pragmatic approach to enrollment and to the delivery of RRT, methods to reduce bias (allocation concealment, objective outcomes, and steps to ensure complete follow-up), recruitment from centers experienced in critical care and RRT research, and incorporation of alternate consent models. These steps will reliably inform decision-making regarding the design of the definitive trial. In addition, our inclusion criteria acknowledge that conventional metrics of kidney function poorly predict the need for RRT. Accordingly, a novel and unique aspect of our trial is the incorporation of a kidney-damage-specific biomarker, NGAL, in the patient selection process.

The design of this pilot RCT has limitations. First, the inclusion criterion of central venous pressure ≥8 mmHg does not reliably identify patients who are adequately volume resuscitated, but this measurement is more likely to be available than other functional hemodynamic assessments [32]. Second, although we have provided general recommendations that reflect prevailing clinical practice and are consistent with current clinical practice guidelines, we have not protocolized other aspects of RRT delivery, such as clearance and modality, in the absence of data confirming the clear superiority of a particular approach [33,34]. Although caregivers are not blinded in this trial, clinician awareness of treatment assignment in two recent RCTs of RRT in the ICU did not compromise study validity [12,25]. Third, it is possible that attending intensivists and nephrologists will have firm beliefs on the timing of RRT initiation and decline to allow their patients to be enrolled. However, a survey of Canadian intensivists and nephrologists (n=180) found that the large majority (93.7%) believed it would be ethical to randomize patients into such a trial [14].

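### The safety outcome, its analysis and the event collection name different event sets, and the outcome's undefined attribution filter may under-count non-fatal harms of deferring RRT

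*Protocol article*

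**What the plan says.** Four places in the protocol article describe the safety events.

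- Primary and secondary outcomes, item 3, gives the outcome: "Serious adverse events potentially attributable to the study treatment, including death, vascular-access complications and complications associated with the delivery of RRT", counted up to day 14. The limiting words are "potentially attributable to the study treatment".
- Analysis gives the comparison: "The secondary safety analysis will evaluate differences in the incidence of adverse events between the accelerated and standard groups". It sets no condition on seriousness, attribution or time window.
- The abstract's Methods/design paragraph lists "safety (occurrence of adverse events" among the secondary outcomes, also without qualification.
- Adverse events describes two collections over 14 days. The first is "Adverse events that are potentially attributable to the study treatment, including death, vascular-access complications" and RRT-delivery complications, which is nearly the list in item 3 but not confined to serious events. The second is broader: "all serious adverse events that occur within 14 days after randomization are to be documented and reported, regardless of direct connection to the study".

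Table 2 sets out the reportable events in two columns, one for RRT and one for the central venous catheter. On who knows the allocation, the Design section calls the trial open-label, and the Discussion says "Although caregivers are not blinded in this trial". Trial oversight gives the DSMB the task of assessing whether events are linked to the trial, as part of its monitoring. No assessor is named for the attribution in item 3.

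**The concern.** There are two linked problems.

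First, the between-arm safety comparison has no single numerator. Item 3, the Analysis section and the Adverse events section would each produce a different count from the same patients. This is a disagreement within the text, not a detail left to a later document.

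Second, if item 3 is followed, an event counts only when it is deemed potentially attributable to study treatment. The trial compares times of starting RRT. Attribution comes easily for a complication of a catheter or a dialysis session. It comes less easily for a complication that arises because RRT had not yet begun. The Background names severe hyperkalemia, profound acidosis and fluid overload with respiratory failure as the dangers that early RRT might avoid. None of these is in Table 2.

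Evaluating safety is a stated purpose of the pilot and feeds the definitive trial. A numerator that picks up harms of starting more readily than non-fatal harms of waiting would be a poor basis for that decision.

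**Working it through.** **1. The event sets side by side**

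| Place | Serious only? | Attributable only? | Window |
|---|---|---|---|
| Abstract | no | no | none given |
| Outcomes, item 3 | yes | yes | day 14 |
| Analysis | no | no | none given |
| Adverse events, first collection | no | yes | 14 days |
| Adverse events, second collection | yes | no | 14 days |

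The abstract and the Analysis section agree with each other. Neither agrees with item 3. The second collection holds the data for an attribution-free comparison of serious events.

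**2. Does the filter depend on arm?**

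- Accelerated arm: RRT is to start within 12 hours of eligibility, so nearly all patients are exposed early to a dialysis catheter and to RRT.
- Standard arm: RRT is deferred, and the outcome text allows that it may never start. The Background puts receipt of RRT in severe AKI at 50 to 70%. If that range carried over to the standard arm (an assumption), 50 × 0.50 = 25 to 50 × 0.70 = 35 of 50 patients would be exposed.
- Table 2 lists severe hypokalemia but not hyperkalemia, and counts arrhythmia only when it develops during RRT. A patient who never receives RRT cannot have an RRT-delivery event.

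So exposure to the listed event types differs by arm by design. A non-fatal harm of deferral enters item 3 only if someone decides that withholding RRT was a study treatment that caused it.

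**3. Size, by illustration**

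The article gives no serious-event rate and no safety power, so there is no stated figure to reproduce. The arm size of 50 follows from n=100 and 1:1 allocation. The event risks and attribution rates below are assumptions. They refer to non-fatal serious events, because death is included under either definition.

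Expected patients counted = 50 × true risk × attribution rate. The true risk is the same in both arms.

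| True risk | Attribution, accelerated v standard | Counted patients | Spurious gap |
|---|---|---|---|
| 30% | 70% v 60% | 10.5 v 9 | 3 points |
| 30% | 60% v 40% | 9 v 6 | 6 points |
| 30% | 80% v 50% | 12 v 7.5 | 9 points |
| 30% | 70% v 30% | 10.5 v 4.5 | 12 points |

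The next table gives the exact probability that a two-sided Fisher test at 0.05 (the test and level in the Analysis section) declares a difference when there is none, with 50 per arm:

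| Attribution | True risk 30% | True risk 50% |
|---|---|---|
| 50% v 50% | 2.4% | 3.0% |
| 60% v 40% | 7.8% | 15.5% |
| 70% v 30% | 28.4% | 56.8% |
| All events counted | 3.1% | 3.5% |

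With equal attribution the filter loses events but does not distort the comparison. The distortion grows only as attribution diverges between arms.

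**4. Precision of the attribution-free comparison**

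The approximate 95% half-width for a risk difference with equal risk p and 50 per arm is 1.96 × √(2p(1−p)/50). At p = 0.30 this is 1.96 × √0.0084 ≈ 18 points. At p = 0.50 it is 1.96 × √0.01 ≈ 20 points. The comparison is imprecise, and an interval shows that better than a P-value alone.

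**The case against.** The strongest reply is that item 3 can be read as a list of event types rather than a case-by-case ruling on cause. It matches the Adverse events section and Table 2, several Table 2 entries have objective thresholds, and death is named. On that reading no one exercises judgement. This stands in part: it removes the worry about subjective attribution for listed events. It does not remove the asymmetry, because the listed types other than death concern RRT and the catheter, and the main non-fatal dangers of waiting are not listed.

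A reader might infer that staff who know the allocation make the attribution. The article does not say so. It says that caregivers are not blinded and names no assessor for this outcome. The only body given a linkage task is the DSMB, as a monitor. The attribution is unspecified, and that is as far as the text goes.

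A reader might also take this to be the trial's only safety comparison. It is not. Mortality, need for RRT and a composite of major adverse kidney events, all through day 90, are compared by arm as tertiary analyses and involve no attribution. A fatal harm of waiting would appear there and in item 3 itself.

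It is also fair to say that more catheter and RRT complications in the accelerated arm would be a genuine consequence of that strategy. They should be shown and not explained away. Finally, if the analysis really uses the unqualified set in the Analysis section, the filter need not enter it. That is correct, and it is why the passages must first be brought into line.

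**Conclusion.** The inconsistency is certain from the text: the abstract, item 3 and the Analysis section do not define one safety event set. The bias is conditional. If item 3 governs, the arm comparison may under-count non-fatal harms of deferral, because the named event types occur mainly in patients who receive RRT and everything else depends on an undefined attribution.

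Its size is unknown. Under the assumed rates above, the spurious gap at 30% risk runs from 3 to 12 points, and it is zero if attribution and listing work equally in both arms. The documents do not support a claim that the safety conclusion would be reversed, or that deaths would be missed. The consequence is moderate, since this is a secondary outcome of a 100-patient pilot. It is still worth correcting, because the data needed are already being collected.

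**What to change.** - Use one safety event set in the abstract, in item 3 of the outcomes and in the Analysis section: the proportion of patients with at least one serious adverse event to day 14, regardless of attribution.
- Compare it by randomized arm with a risk difference and 95% CI, and show all-cause death separately.
- Report the RRT- and catheter-related events of Table 2 by arm alongside it, as real consequences of each strategy.
- If an attributed subset is also reported, say who makes the attribution and whether they know the allocation.

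The cost is a change of wording and one added table, with no new data collection. The drawback is noise: serious events are common in critically ill patients, and background events that timing does not affect will dilute any difference. With about 50 per arm the interval will be wide in any case. Keeping the Table 2 events next to the all-event comparison preserves the more specific information.
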